#### **6.1.6 Serious Adverse Reaction (SAR)**

SAR is any SAE deemed to be **probably related or definitely related** to the study supplementation (as defined above).

Trial recruitment will be stopped with immediate effect if any child has a SAR to any of the iron supplements (or placebo) until review by the DSMB. Follow-up of children already enrolled in the study will continue as planned pending the review of the DSMB, as indicated in the DSMB Charter.

### **6.2 Reporting procedures**

The Local Safety Monitor (LSM) will prepare regular reports concerning AEs and SAEs for submission to the local PI. The local PI (Clinical Trial Coordinator), shall report all SAEs (defined as in 6.1.3) without filtration, whether or not related to the trial intervention, within 24 hours of becoming aware of the event to the Sponsor, through the MRCG CTSO ([contact]), and the LSM. The complete SAE report form will be sent to the DSMB members as soon as the full detailed report is available, usually within 7 days of the study team becoming aware of the event.

If the SAE is related to the trial intervention, the Ethics Committee will be notified within 7 calendar days if fatal or life-threatening, and all others within 15 calendar days.

All SAE will be reported to the Medicines Control Agency in accordance with the applicable requirement.

The minimum information required for this initial SAE report is:

- Trial number and (short) title
- Participant's ID
- Date and time of onset
- Description of the event (clinical history, associated signs and symptoms)
- Reporter's name

The information about which intervention was administered (unblinding) will only be provided at the request of the DSMB.

The local PI will not wait for additional information to fully document the event before notifying the Sponsor and the LSM. The report is then to be followed by submission of a completed SAE Report Form as soon as possible, detailing relevant aspects of the SAE in question. All actions taken by the local PI and the outcome of the event must also be reported immediately.

For documentation of the SAE, any actions taken, outcome and follow-up, the SAE Report Forms will be used. All follow-up activities have to be reported, if necessary on one or more consecutive SAE report forms in a timely manner. All fields with additional or changed information must be completed. Hospital case records and autopsy reports, including verbal autopsy, will be obtained where applicable.

At the request of the DSMB, only final and complete SAE Report Forms, including follow-up actions, will be sent to notify them of an SAE. This notification will occur usually within 7 days of completion of the final report.

### **6.3 Safety oversight**

Safety oversight shall be provided by a DSMB who will provide independent advice as stipulated in Section 6 above. An independent Local Safety Monitor will review all adverse events more regularly and report regularly to the PIs and DSMB.

## **7 Discontinuation criteria**

## **7.1 Participant's premature termination**

Mothers/guardians of participating children have the right to stop their children's participation in the study at any time without giving a reason and this will not affect the medical care that would normally be received. The trial team may also withdraw a participant from the study if deemed necessary at any time taking in to consideration the reasons mentioned below. The reason for a participant's premature termination will be documented on the appropriate page of the CRF and specified which of the following possible reasons were responsible for the premature termination:

- Serious Adverse Event
- Adverse Event
- Participant's consent withdrawal
- Development of withdrawal criterion
- Protocol deviation
- Migrated/moved from the study area
- Lost to follow-up

A 'lost to follow-up' is any participant who completed all protocol specific procedures up to the administration of the investigational product or intervention, but was then lost during the study period to any further follow-up, with no safety information and no efficacy endpoint data ever became available.

In case the participant decides to withdraw participation or consent during the study, we will not work on participant's samples without permission, but any information already generated from the samples will be kept and used. The study clinician may also ask for tests for the participant's safety. The PI will inquire about the reason for any withdrawal and follow-up with the participant regarding any unresolved AEs.

For withdrawn participants no specific data will be collected. Our sample size takes into account a dropout rate of 15% but this will be monitored closely and if the observed dropout rate increases above this level we will replace subjects to ensure we reach our target sample size of n=600 completed.

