### **4.3 Withdrawal of participants**

A study participant will be discontinued from the study intervention if:

- Hb concentration falls < 7 g/dL
- Any clinically-significant adverse event (SAE), laboratory abnormality, intercurrent illness, or other medical condition or situation occurs such that continued participation in the study would not be in the best interest of the participant
- Development of a chronic disease
- Participation in another study

Note that there is no formal withdrawal criteria for participants that develop moderate-severe diarrhoea episodes since this is a primary outcome of the trial. However, children that show clear signs of infectious diarrhea, such as blood or mucus in the stool, will be provided with appropriate treatment and the causative agent for the infection will be determined using stool microbiology and the TaqMan Array Card (TAC) system (41).

Participants are free to withdraw from the study at any time without giving a reason.

Participants who discontinue study intervention due to severe anaemia (Hb<7 d/dL) will be offered standard-of-care treatment according to the national guidelines and will continue to be followed up by the study clinical team at the weekly clinics. These children will not be excluded from the data analysis and will be treated as treatment failures.

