#### **5.1.5 Early termination visit**

An early termination visit may occur in this study because of a participant's voluntary withdrawal, trial team decision or at the discretion of the Data Safety Monitoring Board as described in Section 7. Apart from the safety evaluations, no other evaluations required for the final study visit will be done.

[figure not shown]

**Figure 5. Study Flow Chart.** Abbreviations: Hb, haemoglobin; Ft, ferritin; RDT, rapid diagnostics test; STH, soil-transmitted helminths; AE, adverse events; SAEs, serious adverse events; FA, field assistant; Fe, iron.

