## 8.2 Statistical analysis

The data analysis plan will be fully developed prior to database lock and will be done with the expert input from [name] of the MRC Biostatistics Unit in Cambridge. Briefly, for the primary analysis, we will fit a logistic regression to the efficacy outcome data, adjusting for the strata created by age and Hb level groups prior to enrolment. The odds ratio for effect of IHAT relative to ferrous sulphate will be estimated, and if the lower 90% one-sided confidence interval is above 0.583 (equivalent to the 10% non-inferiority margin above), non-inferiority will be declared for IHAT. The diarrhoea endpoint will be analysed in a similar way, but tested for superiority (i.e. if the one-sided p-value for the Wald test of the effect of IHAT is less than 0.1) for the comparison between IHAT and ferrous sulphate. For the primary non-inferiority hypothesis we will conduct per-protocol and intention-to-treat analyses and for the superiority hypotheses we will conduct intention-to-treat analyses.

The secondary endpoints (calprotectin, NTBI etc) will be tested using linear regression with the same covariates. Morbidity data will be analysed using multiple regression analysis controlling for possible confounders.

In relation to the microbiome data analysis we will work together with our collaborators in the Sanger Institute and use the most up to date bioinformatics methodology available at the time of data analysis to investigate the impact of treatment arm and time in the composition of the gut microbiome. Since this analysis will only occur in late 2018/early 2019, it is premature to decide the strategy for data analysis now as this is a fast moving field with new and better bioinformatics tools becoming available every couple of months. The Sanger Institute works very closely with the European Bioinformatics Institute (EBI) (housed in the same campus) to ensure they use the very latest tools in their microbiome analysis.

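### Section 7.1 ends data collection for children the team withdraws, while 4.3 promises follow-up only after Hb<7 g/dL, so the intention-to-treat analyses in 8.2 can lack outcomes

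*Supplement*

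**What the plan says.** All references are to the latest protocol version in the Supplement.

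- **Section 4.3** opens its list of stopping rules with "A study participant will be discontinued from the study intervention if". The list covers Hb<7 g/dL, a clinically significant adverse event or intercurrent illness, a chronic disease, and joining another study. Only for the Hb<7 g/dL group does it add that the children "will continue to be followed up by the study clinical team at the weekly clinics" and are analysed as treatment failures. It also says that moderate-severe diarrhoea is not a formal reason for withdrawal, because it is a primary outcome.
- **Section 7.1** says: "The trial team may also withdraw a participant from the study if deemed necessary at any time". Its listed reasons include serious adverse event, adverse event, development of a withdrawal criterion and protocol deviation, besides withdrawn consent, migration and loss to follow-up. It then says "For withdrawn participants no specific data will be collected". Information already generated from samples is kept, and unresolved adverse events are followed. If dropout exceeds 15%, children are replaced until 600 have completed.
- **Section 5.1.5**, on the early termination visit: "Apart from the safety evaluations, no other evaluations required for the final study visit will be done".
- **Section 8.2**: "For the primary non-inferiority hypothesis we will conduct per-protocol and intention-to-treat analyses and for the superiority hypotheses we will conduct intention-to-treat analyses".

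**The concern.** An intention-to-treat analysis compares children as randomised, whatever happens to their treatment, so it needs outcomes from children who have stopped the supplement. Section 4.3 reads as though stopping the supplement leaves a child in the study. Section 7.1 names the development of a withdrawal criterion as a reason for premature termination and then stops data collection. A child stopped under 4.3 for anything other than Hb<7 g/dL may thus be followed or lost, depending on which section the field team applies. A child withdrawn for an adverse event or a protocol deviation loses outcome follow-up even where the family would have stayed.

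What is at stake differs by hypothesis. For efficacy non-inferiority (hypothesis 1), the Day 85 response is missing. For diarrhoea incidence (hypothesis 2), episodes after withdrawal are missing. For diarrhoea period prevalence (hypotheses 3 and 4), only first episodes in children withdrawn before having any are missing. If adverse events or deviations are more frequent in one arm, the losses are unequal in number or in kind, and topping up the number of completers does not restore the randomised comparison.

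**Working it through.** **1. The plan's own figures.** Inputs: 600 completers, 15% non-completion, 705 enrolled, 235 per arm (3.1, 7.1, 8.1).

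- Enrolment: 600/(1 − 0.15) = 706, against 705 stated. Conversely, 705 × 0.85 = 599 and 235 × 0.85 = 199.75, so the 200 per arm in 8.1 are completers.
- Hypothesis 1 power, Wald test on the log odds ratio with response 0.3 in both arms, limit 0.583, one-sided 10%: SE = √(2/(200 × 0.3 × 0.7)) = 0.218; −ln 0.583 = 0.540; Φ(0.540/0.218 − 1.282) = 0.883, against 89% stated.
- Hypothesis 3 power, 0.15 against 0.25: SE = √((0.15 × 0.85 + 0.25 × 0.75)/200) = 0.0397; Φ(0.10/0.0397 − 1.282) = 0.892, against about 90% stated.

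The calculations reproduce, and they treat the 15% purely as lost numbers, with no allowance for who is lost.

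**2. Who is followed after stopping.**

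| Reason for stopping | Section 4.3 | Section 7.1 | Outcome follow-up |
|---|---|---|---|
| Hb<7 g/dL | stops intervention; followed; counted as failure | withdrawal criterion | stated |
| Clinically significant adverse event or illness | stops intervention | possible withdrawal from study | not stated in 4.3; none if withdrawn under 7.1 |
| Chronic disease, other study | stops intervention | withdrawal criterion | same |
| Protocol deviation | not listed | possible withdrawal from study | none if withdrawn |

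**3. Number affected.** 0.15 × 235 = 35 per arm at most. The 15% is total non-completion, so the share due to adverse events, withdrawal criteria and deviations is some unknown part of it.

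**4. Bias.** Let w be the fraction unobserved in each arm, D_obs the arm difference in observed children and D_un that in unobserved children. The full difference is (1 − w)D_obs + w·D_un, so an analysis of observed children is off by w(D_obs − D_un). The 20-point departure is an assumption; 10 points is shown beside it.

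| w | 10-point departure | 20-point departure |
|---|---|---|
| 5% | 0.5 points | 1 point |
| 10% | 1 point | 2 points |
| 15% (upper bound) | 1.5 points | 3 points |

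Three points is 30% of the 10-point margins in hypotheses 1 and 4, and 0.03/0.0397 = 0.76 standard errors for hypothesis 3.

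**5. What the data could not exclude.** With 30% response among observed children and 15% missing, an arm's true response lies between 0.85 × 0.30 = 25.5% and 25.5% + 15% = 40.5%.

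**6. Error rates under assumed loss patterns** (15% lost, 200 analysed per arm; the patterns are assumptions).

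- Hypothesis 1 at its null (0.20 against 0.30), with random losses on ferrous sulphate and IHAT non-responders lost 1, 1.5, 2 or 3 times as often as responders: one-sided type I error 0.10, 0.16, 0.19 or 0.24. For a ratio of 2, responders are lost at 0.15/(0.2 + 0.8 × 2) = 0.083 and non-responders at 0.167, so the observed IHAT response is 0.2 × 0.917/0.85 = 0.216.
- Hypothesis 3, with ferrous sulphate children who would be cases lost 1, 1.5, 2 or 3 times as often as the others: power 0.89, 0.81, 0.73 or 0.57. This overstates the route in question, since a child with a recorded episode already counts. If the same ratio holds in both arms, power stays at 0.88 to 0.89.

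**The case against.** The strongest reply is that the text promises less loss than this suggests, and much of it stands.

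- A reader might infer that the intention-to-treat analyses cannot be done. The documents do not support that. Data up to withdrawal exist, Hb<7 g/dL failures are followed and counted, and an analysis with a stated missing-data method is feasible. The data analysis plan is not shown and may define one. It cannot recover outcomes never collected.
- A reader might infer that the children worst affected by diarrhoea vanish from the data. A child withdrawn for moderate-severe diarrhoea has already had the episode recorded as an adverse event (2.1, 6.1.1) and is a case for period prevalence; only repeat episodes are lost. Section 4.3 also sets no formal diarrhoea withdrawal criterion.
- A reader might take 5.1.5 as cancelling Day 85 sampling. It concerns evaluations belonging to the final study visit, which 5.1.4 places on Day 113 with a finger prick. It needs aligning but is not the source of the gap.
- Replacement might be read as routine. It applies only if dropout exceeds 15%.
- Team withdrawal is permissive, and 9.3 answers deviations with corrective action and documentation. So the text does not show that deviators will be dropped, only that they may be.
- The data-collection sentence follows a paragraph on families who withdraw participation or consent, and could be meant for them alone. But it is worded for withdrawn participants in general and sits beside the overall dropout allowance. That is a reason to reword it.

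**Conclusion.** The point holds as a conflict between stated rules. Section 7.1 permits team-initiated withdrawal for adverse events, withdrawal criteria and deviations and ends data collection. Section 4.3 ends only the intervention and secures follow-up for one group. Section 8.2 relies on intention-to-treat. The main exposure is the Day 85 response in hypothesis 1 and later episodes in hypothesis 2, with a smaller part in hypotheses 3 and 4.

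The documents show that losses could depend on arm or outcome, not that they will. The size is unknown. The 3-point figure rests on two assumptions: that the whole 15% arises by this route, which overstates it, and that the arm differences in unobserved and observed children are 20 points apart. The change should be made because it is cheap and the missing outcomes cannot be recovered afterwards.

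**What to change.** Reconcile 4.3, 5.1.5 and 7.1 so that stopping the supplement and leaving the study are separate events, recorded separately. Replace the data-collection sentence in 7.1 with wording such as: children who stop the supplement, including for an adverse event or a protocol deviation, stay in outcome follow-up (morbidity records and Day 85 samples) unless consent for follow-up is withdrawn, the child moves away, or the clinician considers continued procedures not to be in the child's interest. This extends the approach already taken for Hb<7 g/dL and alters no treatment-stopping rule.

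The cost is protocol wording and a few extra visits and sample sets. Field workers already visit study children daily and the Day 85 clinics run anyway. At the planned rate the ceiling is 705 × 0.15, about 106 children across the trial, less those who move, refuse or cannot be traced. Following all 235 per arm would raise hypothesis 1 power from 0.883 to 0.919 by the same formula, which is the most that could be gained.

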## **7.2 Study discontinuation**

The rules for study termination will be set by the DSMB at their first meeting.

## **8 Statistical considerations**

### **8.1 Sample size determination**

This section was prepared with the expert input of [name], MRC Biostatistics Unit, Cambridge. [name] is a Programme Leader Track senior statistician who primarily works on statistical methodology for novel clinical trial designs and is one of the few UK experts in design and analysis of adaptive clinical trials. [name] is a long term collaborator of [name] for the design of the IHAT trials and is a collaborator in the proposed trial. He has provided advice on the trial design and conducted the trial power modelling and sample size calculations presented in this Section. [name] will continue to provide advice on the trial design to the PIs and will supervise an MRCG statistician in the data analysis corresponding to the four trial hypothesis (below). [name] will be a member of the TSC and will review and approve the data analysis plan for the trial, but it will be the responsibility of the MRCG statistician ([name] supervised by [name]) to develop the initial drafts of the data analysis plan together with the study PIs.

#### **There are four null hypotheses in the study:**

- 1) non-inferiority of IHAT compared to ferrous sulphate for efficacy (in terms of Hb and iron deficiency correction: i.e. IDA) response probability (or prevalence). In this case we are testing the null hypothesis that: response in the IHAT arm minus the response probability in the ferrous sulphate arm is less than or equal to  $-0.1$ . We define 'response' for IDA as correction of iron deficiency and either achieving a normal Hb or an increase of at least 1 g/dL after 12 weeks of iron supplementation.
- 2) superiority of IHAT compared to ferrous sulphate in terms of incidence density of diarrhoea. Here the null hypothesis is that the mean number of new episodes in the IHAT arm is greater than or equal to the mean number in the FeSO4 arm.
- 3) superiority of IHAT compared to ferrous sulphate in terms of prevalence of diarrhoea. Here the null hypothesis is that the prevalence of diarrhoea in the IHAT arm is greater than or equal to the prevalence in the FeSO4 arm.
- 4) non-inferiority of IHAT compared to placebo in terms of prevalence of diarrhoea. Here the null hypothesis is that the prevalence of diarrhoea in the placebo arm minus the prevalence in the IHAT arm is less than or equal to  $-0.1$ .

Because this is a pilot study we do not formally adjust for multiple testing due to the four hypotheses. This is because any significant results will be tested again in a pivotal study.

The trial is powered to show non-inferiority of IHAT relative to ferrous sulphate for the 12 weeks efficacy response probability. At the 12 weeks time-point (i.e. Day 85), the estimated odds ratio between the IHAT and FeSO4 arms will be calculated, together with a 90% one-sided confidence interval. If the lower limit of the confidence interval for this difference is above 0.583 (equivalent to a 10% absolute difference if FeSO4 response rate is 0.3), then non-inferiority of IHAT in terms of efficacy will be declared.

Because many trials conducted in Africa and other developing countries with the gold standard ferrous sulphate or ferrous fumarate supplementation still fail to provide anaemia resolution in interventions shorter than 6 months, we have considered here that an increase of 1 g/dl in Hb after 3 months is an indication of efficacy, even though we accept that this is not clinical efficacy. We have based our assay sensitivity from data published with relevant iron supplement studies in children available in the literature (3, 7, 52). We plan, however, to use the data collected in the proposed study to conduct an exploratory analysis to test for assay sensitivity. These data will be very useful so that adequate treatment effect sizes can be used to power any future studies, in particular a pivotal trial, both for ferrous sulphate and IHAT supplementation effects.

Due to this trial being a pilot study, any significant results will be re-tested in the pivotal 'full' trial (BMGF full award). Thus, we considered a larger than traditional type-I error rate of 10%. Assuming that 30% (i.e. a response probability of 0.3) of the children in both arms will resolve iron deficiency and either achieve a normal Hb or an increase of at least 1 g/dL after 12 weeks of iron supplementation (3, 7, 52), then a sample size of 200 in the IHAT arm and 200 in the ferrous sulphate arm will provide 89% power to show non-inferiority with a non-inferiority margin of 0.1 (0.583 on the odds-ratio scale). In other words, the trial will have 89% power (at a 10% one-sided significance level) to show that the lower boundary of the confidence interval of the odds ratio between IHAT and ferrous sulphate is more than 0.583 at 12 weeks.

We have based our calculation above on assay sensitivity data taken from other studies with iron supplements reported in the literature, but we will also perform an exploratory analysis to test for assay sensitivity, and this information will be used to power the potential future pivotal study.

We have considered two options for modelling the diarrhoea outcome: 1) 'period prevalence', i.e. the proportion of children with at least one episode of moderate-severe diarrhoea over the 12 weeks intervention period; 2) 'incidence density'. i.e. the number of new diarrhoea episodes per child over the 12 weeks intervention period. The modelling of how the power of the trial varies according to assumptions for each of these outcomes is detailed below.

The trial sample size will also provide 90% power to show superiority of IHAT in terms of moderate-severe diarrhoea 'incidence density', assuming that IHAT provides a 20% reduction in mean moderate-severe diarrhoea 'incidence density' relative to ferrous sulphate; and 90% power to show superiority of IHAT in terms of 'period prevalence' of moderate-severe diarrhoea, assuming that 25% of children will develop moderate-severe diarrhoea episodes with ferrous

sulphate and 15% will have moderate-severe diarrhoea with IHAT over the 12 weeks intervention. For the comparison between the IHAT and placebo arms, the trial is powered to show non-inferiority of IHAT relative to placebo, for example, the trial will have 93% power for the moderate-severe diarrhoea 'period prevalence' outcome. All the assumptions for these calculations were based on data from studies conducted in The Gambia for the same age group, please refer to the extra information below for further details.

As part of the rationale for the study is to provide information for a pivotal study, we also examined the precision that the sample size would provide on the confidence interval width of the outcomes considered. Since the width of the confidence interval is highly dependent on the proportion in the control group as well as the true odds ratio, we consider several different values in the table below.

| Binomial proportion in control group | True odds-ratio | 95% confidence interval width |
|--------------------------------------|-----------------|-------------------------------|
| 0.1                                  | 0.5             | 0.85                          |
|                                      | 1               | 1.38                          |
|                                      | 1.5             | 1.91                          |
| 0.3                                  | 0.5             | 0.49                          |
|                                      | 1               | 0.88                          |
|                                      | 1.5             | 1.27                          |
| 0.5                                  | 0.5             | 0.42                          |
|                                      | 1               | 0.80                          |
|                                      | 1.5             | 1.21                          |

The power calculations for some of the secondary outcomes are also presented in more detail below. Briefly, the trial (n=200 per arm) will have over 85% power to detect significant differences between all the arms in terms of Enterobacteria, NTBI and calprotectin.

Taking into consideration a non-completion rate of 15% (this is based on data from previous studies in The Gambia), we expect to **enrol 705 children in the study**.

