### There are four null hypotheses in the study:

1) non-inferiority of IHAT compared to ferrous sulphate for efficacy (in terms of Hb and iron deficiency correction: i.e. IDA) response probability (or prevalence). In this case we are testing the null hypothesis that: response probability in the IHAT arm minus the response probability in the ferrous sulphate arm is less than or equal to  $-0.1$ . **We define 'response' for IDA as correction of iron deficiency and either achieving a normal Hb or an increase of at least 1 g/dL after 12 weeks of iron supplementation.**

2) superiority of IHAT compared to ferrous sulphate in terms of incidence density of diarrhoea. Here the null hypothesis is that the mean number of new episodes in the IHAT arm is greater than or equal to the mean number in the  $\text{FeSO}_4$  arm.

3) superiority of IHAT compared to ferrous sulphate in terms of prevalence of diarrhoea. Here the null hypothesis is that the prevalence of diarrhoea in the IHAT arm is greater than or equal to the prevalence in the  $\text{FeSO}_4$  arm.

4) non-inferiority of IHAT compared to placebo in terms of prevalence of diarrhoea. Here the null hypothesis is that the prevalence of diarrhoea in the placebo arm minus the prevalence in the IHAT arm is less than or equal to  $-0.1$ .

**The primary objective for this trial is to show non-inferiority of IHAT in relation to ferrous sulphate at correcting IDA, and in terms of diarrhoea to show superiority in relation to ferrous sulphate and non-inferiority in relation to placebo (as defined above).** Secondary objectives are to show that IHAT is non-detrimental with respect to enteric pathogen burden, the gut microbiome, and intestinal inflammation.

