## II. POWER of the trial for the secondary endpoints

1) Microbiome (Enterobacteria log10 counts):

We based our calculation on the data for Enterobacteria (the genus that contains most enteropathogens including *E. coli*) reported in Zimmermann 2014 study conducted with 4 months supplementation (8): with iron 8.9 (0.3) and without iron 8.0 (0.4). Taking into consideration that in this study the analysis combined the groups with 2.5 mg Fe and 12.5 mg Fe MNP, then the combined sample size implies an individual standard deviation of 3 for the Enterobacteria and assuming a 0.9 difference between the groups and a superiority margin of 0.2 (i.e. an absolute difference in Enterobacteria between the IHAT and ferrous sulphate arms of - 0.2), the sample size of 200 children per group would give us 85% (at 10% one-sided significance level).

2) Calprotectin

Again, we based this calculation in the Zimmermann 2014 study (8). Calprotectin concentration with iron: 248.9 +/- 2.2 µg/g and without iron: 102.5 +/- 2.2 µg/g in the 12.5 mg MNP. Here the individual SD should be around 11.8 considering the study sample size in the 12.5mg Fe MNP group, which would mean that with 200 per arm we could detect an absolute mean difference of 3 with 90% power (10% one-sided sig level) and with 50 per arm we would be able to detect a mean difference of 6.1.

3) NTBI

For this calculation we have used the 'normal serum' data provided by [name] with the same method we intend to use in the study (44). Taking the values reported in the paper for 'normal serum' of 0.24 +/- 0.15 (mean +/- SD), n=9 range 0.04 – 0.41, the individual standard deviation would be 0.45. There is no published data with this method for NTBI after an iron dose so we have assumed we would like to detect a mean difference of 0.5 between the IHAT and the ferrous sulphate arm, which would mean that with 50 per arm the power would be more than 90%. To be able to detect smaller differences with this method we would need to increase sample size.

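### Section 8.1 claims over 85% power for Enterobacteria across every pair of arms, but its inputs support this for IHAT vs ferrous sulphate and ferrous sulphate vs placebo, not for IHAT vs placebo

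*Supplement*

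**What the plan says.** Section 8.1 of the protocol (Sample size determination) summarises the secondary outcomes in one sentence. With 200 children per arm, the trial "will have over 85% power to detect significant differences between all the arms in terms of Enterobacteria, NTBI and calprotectin". The sentence gives no effect size and refers the reader to the details that follow.

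Those details are in part II of the same section, on power for the secondary endpoints. The Enterobacteria item takes its means from a cited four-month iron fortification study: 8.9 log10 with iron and 8.0 without. It says that the combined sample size "implies an individual standard deviation of 3 for the Enterobacteria", and it calculates power "assuming a 0.9 difference between the groups and a superiority margin of 0.2". The margin is explained as "an absolute difference in Enterobacteria between the IHAT and ferrous sulphate arms of - 0.2", and IHAT vs ferrous sulphate is the only contrast named. The stated result is 85% power with 200 per group at a one-sided 10% level.

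The NTBI item also names one contrast: "we would like to detect a mean difference of 0.5 between the IHAT and the ferrous sulphate arm". The calprotectin item gives a detectable difference and names no contrast.

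Section 2 sets the aim these outcomes serve: "Secondary objectives are to show that IHAT is non-detrimental with respect to enteric pathogen burden, the gut microbiome, and intestinal inflammation".

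**The concern.** Three arms have three pairwise contrasts, and the summary sentence covers all of them. The Enterobacteria calculation contains a single difference, that between iron and no iron. If the whole of it separates IHAT from ferrous sulphate, nothing is left to separate IHAT from placebo. If part of it separates IHAT from placebo, less is left for IHAT vs ferrous sulphate. Either way, high power for both IHAT contrasts looks unattainable.

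This matters because IHAT vs placebo bears most directly on whether IHAT is harmless to the gut microbiome. Sections 3.1 and 5.1.3 give ruling out harm, including to the microbiome, as a main reason for having a placebo arm. The target product profile in Appendix 2 counts the absence of a significant Enterobacteria increase as its minimum acceptable result, though it names no comparator. A reader who believed that every pair had over 85% power could take a non-significant IHAT-placebo result as good evidence of no effect, and the calculation does not support that.

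**Working it through.** **Inputs**, all from Section 8.1: SD 3; 200 per arm after allowing for 15% non-completion; one-sided 10% level, so z = 1.2816; means of 8.9 with iron and 8.0 without, so a difference of 0.9; superiority margin 0.2.

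**Formulas** (normal approximation):

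- SE of a difference between two arms = 3 × √(2/200) = 0.30.
- Power = Φ((difference − margin)/0.30 − 1.2816).

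**Reproducing the plan's figure.** For IHAT vs ferrous sulphate: (0.9 − 0.2)/0.30 − 1.2816 = 1.052, and Φ(1.052) = 85.4%. A t-test calculation gives 85.3%. The plan's 85% is therefore correct for its stated inputs. Without the margin the power is 95.7%.

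**Ferrous sulphate vs placebo.** The 0.9 is itself an iron vs no-iron difference, so it applies here directly. Power is again 85.4% with the margin and 95.7% without.

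**IHAT vs placebo.** The plan gives no difference for this pair. Hold placebo at 8.0 and ferrous sulphate at 8.9, and let IHAT sit at points between them:

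| IHAT minus placebo | IHAT vs placebo: no margin | with 0.2 margin | Ferrous sulphate minus IHAT | IHAT vs ferrous sulphate: no margin | with 0.2 margin |
|---|---|---|---|---|---|
| 0 | 10.0% | 2.6% | 0.9 | 95.7% | 85.4% |
| 0.2 | 26.9% | 10.0% | 0.7 | 85.4% | 65.0% |
| 0.45 | 58.6% | 32.7% | 0.45 | 58.6% | 32.7% |
| 0.7 | 85.4% | 65.0% | 0.2 | 26.9% | 10.0% |
| 0.9 | 95.7% | 85.4% | 0 | 10.0% | 2.6% |

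The first row is what the plan's own calculation implies, because it gives IHAT vs ferrous sulphate the full 0.9. The other rows are assumptions that show the range.

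**Can all three pairs reach 85%?** With z(0.85) = 1.0364, the gap needed without a margin is 0.30 × (1.2816 + 1.0364) = 0.695. With the 0.2 margin it is 0.895. If IHAT lies between the other two arms, its two gaps add up to 0.9. Both would have to be at least 0.695, which needs a total of 2 × 0.695 = 1.39. So no IHAT mean between 8.0 and 8.9 gives 85% for all three pairs, with or without the margin.

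**Precision for IHAT vs placebo.** The expected 95% half-width is 1.96 × 0.30 = 0.588, or about 0.59 log10.

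**NTBI check.** With SD 0.45 and 50 per arm, SE = 0.45 × √(2/50) = 0.09. The assumed difference of 0.5 then has over 99.9% power. With 200 per arm, SE = 0.045 and the gap needed for 85% is 0.045 × 2.318 = 0.10.

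**The case against.** The best defence is that power is always conditional on an assumed difference. With equal arms, one SD and one test level, any two arms that truly differ by 0.9 would be separated with about 85% power, whichever two they are. A test of difference always has power equal to its error rate when the true difference is zero, so the 10% is no defect of this design. The summary sentence is expressly brief, and the contrast is named in the detail. The outcomes are secondary, in a trial the protocol calls a pilot. Section 8.2 contains no rule that treats a non-significant IHAT-placebo result as proof of safety, and it defers the microbiome analysis strategy. For diarrhoea the plan uses a non-inferiority approach for this same pair, so its authors know the distinction.

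Much of this stands, and it limits the point to the scope of one sentence. It does not rescue that sentence, which states no conditional difference. The only Enterobacteria difference supplied cannot separate IHAT from both other arms while IHAT lies between them.

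A reader might be tempted by stronger readings that the documents do not support:

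- That the inputs support IHAT vs ferrous sulphate alone. It is the only contrast named, but the 0.9 fits ferrous sulphate vs placebo at least as directly.
- That the protocol states a zero IHAT-placebo difference. It gives no figure. Zero is inferred from the use of the full 0.9 and is consistent with the non-detrimental objective.
- That the plan claims all three tests will be significant together. It makes no joint claim.
- That NTBI is underpowered. No shortfall is shown; the NTBI item simply names one contrast.

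**Conclusion.** The point holds as a matter of scope. The 85% is calculated correctly and applies to two of the three Enterobacteria contrasts: IHAT vs ferrous sulphate and ferrous sulphate vs placebo. It does not extend to IHAT vs placebo. For that pair, power to detect a difference is 10% if IHAT behaves like no iron, as the plan's calculation implies, and about 59% without the margin if IHAT lies midway. In the midway case the IHAT vs ferrous sulphate power also falls to about 59% without the margin, or 33% with it.

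These figures rest on the plan's SD of 3, on 200 completers per arm and on the one-sided 10% level. The impossibility of 85% for all three pairs further assumes that IHAT's mean lies between 8.0 and 8.9. The sample size and the primary hypotheses are not affected.

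**What to change.** In Section 8.1, replace the Enterobacteria part of the summary sentence with wording such as: *about 85% power for IHAT vs ferrous sulphate and for ferrous sulphate vs placebo, assuming a 0.9 log10 difference, SD 3 and a 0.2 margin (200 per arm, one-sided 10%)*. Then add: *no power is claimed for detecting a difference between IHAT and placebo; this contrast will be reported as an estimate with its confidence interval (expected 95% half-width about 0.59 log10)*.

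For NTBI, state the assumed difference (0.5) and the contrast used (IHAT vs ferrous sulphate). Nothing more is needed there.

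No separate analysis plan is shown. Section 8.2 says that it will be completed before database lock, so the same wording can be carried into it. The cost is a few lines of text and a less favourable power statement, with no extra children, samples or assays.
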